## Abstract

**Introduction:**

Digital trials are a promising strategy to increase the evidence base for common interventions and may convey considerable efficiency benefits in trial conduct. Although paediatric intensive care units (PICUs) are rich in routine electronic data, highly pragmatic digital trials in this field remain scarce. There are unmet evidence needs for optimal mechanical ventilation modes in paediatric intensive care. We aim to test the feasibility of a digital PICU trial comparing two modes of invasive mechanical ventilation using carbon dioxide (CO_2_) control as the outcome measure.

**Methods and analysis:**

Single-centre, open-labelled, randomised controlled pilot trial with two parallel treatment arms comparing pressure control versus pressure-regulated volume control. Patients are eligible if aged <18 years, weighing >2 kg, have an arterial line and require >60 min of mechanical ventilation during PICU hospitalisation at the University Children’s Hospital Zurich. Exclusion criteria include cardiac shunt lesions, pulmonary hypertension under treatment and intracranial hypertension. CO_2_ is measured using three methods: end-tidal (continuous), transcutaneous (continuous) and blood gas analyses (intermittent). Baseline, intervention and outcome data are collected electronically from the patients’ routine electronic health records. The primary feasibility outcome is adherence to the assigned ventilation mode, while the primary physiological outcome is the proportion of time spent within the target range of CO_2_ (end-tidal, normocarbia defined as CO_2_ ≥ 4.5 and ≤ 6 kPa). Both primary outcomes are captured digitally every minute from randomisation until censoring (at 48 hours after randomisation, extubation, discharge or death, whichever comes first). Analysis will occur on an intention-to-treat basis. We aim to enrol 60 patients in total. Recruitment started in January 2024 and continued for 9 months.

**Ethics and dissemination:**

This study received ethical approval from the Cantonal Ethics Commission of Zurich (identification number: 2022–00829). Study results will be disseminated through publication in a peer-reviewed journal and other media like podcasts.

**Trial registration number:**

NCT05843123.

STRENGTHS AND LIMITATIONS OF THIS STUDYThis study compares two commonly used modes of invasive mechanical ventilation in a randomised design, providing feasibility data to inform the conduct of digital trials by using electronic patient data directly extracted from the source systems, minimising manual data collection and associated bias and thereby increasing local readiness for more efficient clinical trial conduct.The outcomes of this pilot trial focus on feasibility and physiological measures, with the sample size allowing the assessment of feasibility and exploration of physiological findings, to guide the design and inform power calculations of future larger trials, which should also investigate patient-centred outcomes, age-related differences and longer follow-up time.Blinding is not possible due to the nature of the intervention.Technical issues that may affect the availability or accuracy of data may arise and will be documented.Some aspects of digital trials, such as electronic informed consent, are not implemented in this trial.

## Introduction

 Trials using digital recordings of routine clinical data have great potential to decrease the resources required to conduct clinical trials, which remain one of the major obstacles to faster evidence generation in clinical care. The coronavirus disease pandemic has demonstrated the need for rapid implementation of clinical trials in intensive care, particularly including platform or adaptive designs.^1 2^ Advantages of digital clinical trials include facilitation of recruitment, optimisation of prospective data collection, workflows and monitoring, as well as innovative methods to automate processes, make predictions or assist in phenotyping and result interpretation.^3^ Intensive care units represent an attractive setting for digital trials given the rich data environment with high temporal resolution.^4^

Approximately one in three children receives invasive mechanical ventilation when admitted to paediatric intensive care units (PICUs).^5^ Invasive mechanical ventilation can save lives while bearing risks of ventilator-induced lung injury.^6^ Other negative aspects directly related to invasive mechanical ventilation include ventilator-associated events such as ventilator-associated pneumonia and pneumothorax, side effects of sedation such as neurotoxicity, withdrawal and delirium, and family burden due to disruptive interactions. Mechanical ventilation’s main goal is to provide appropriate gas exchange. Suboptimal mechanical ventilation may lead to fluctuations in carbon dioxide (CO_2_) with associated changes in cerebral and pulmonary blood flow.^7^ These changes can aggravate cerebral ischaemia or swelling and pulmonary arterial hypertension. Prolonged intubation and delayed weaning increase the risk of chronic lung disease, prolonged PICU stay, critical illness neuromyopathy and worse patient-centred outcomes.^8^

It is not known which ventilation mode is most effective with the least harm in children, despite recent technological advances in paediatric mechanical ventilation and the availability of digital ventilation monitoring data.^9^ Classical ventilation modes include conventional pressure-controlled (PC) and volume-controlled modes. Modern ventilators offer algorithm-based adaptive ventilation modes to maximise lung protection.^10^ Pressure-regulated volume control (PRVC) is one such adaptive mode that aims to achieve optimal oxygenation and lung recruitment at lower mean airway pressures (MAP) while maintaining a defined tidal volume.^7^ These adaptive modes rapidly adjust to changes in lung compliance, thereby reducing lung injury, providing a stable minute volume, and stabilising gas exchange. In a Cochrane review, neonates (mostly preterm or low birth weight) ventilated with PRVC modes had lower rates of death or bronchopulmonary dysplasia, pneumothorax, hypocarbia, severe cranial ultrasound pathologies and duration of ventilation compared with infants ventilated with PC modes.^11^ However, there is insufficient evidence to determine the best ventilation mode in critically ill children, and clinicians’ choice is often based on personal or institutional preference.^9 12^

### Aims and hypothesis

The aims of this study are to test the feasibility of a digital trial in the PICU setting, comparing two modes of invasive mechanical ventilation, PC versus PRVC, using CO_2_ levels as the outcome measure. We hypothesise that a digital interventional trial comparing two modes of ventilation in the PICU is feasible and that children will spend more time in normocarbia when ventilated using the PRVC mode compared with the PC mode.

## Methods

### Study design and setting

This study is a pilot, interventional, single-centre, open-label, randomised controlled clinical trial to assess the feasibility of a digital PICU trial. The trial is conducted in the PICU of the University Children’s Hospital Zurich, Switzerland, and is overseen by the Children’s Research Centre monitor. This trial serves to evaluate feasibility, test procedures and obtain parameter estimates that will inform the design and the sample size of future trials. The study was initially planned to begin recruitment in June 2023 and expected to conclude within 6 months by December 2023, whereas actual recruitment started in January 2024 and was expected to be completed in July 2024. This protocol manuscript was submitted on 29 March 2024. Study recruitment was completed during the peer-review process; however, no changes were made to the protocol. We follow Standard Protocol Items for Randomised Trials reporting guidelines.^13^

### Participants, screening and consent procedures

Mechanically ventilated children who are younger than 18 years are eligible for randomisation if their weight is above 2 kg, and if they have an arterial line. Patients who have been ventilated for longer than 24 hours, and those with cyanotic heart disease, pulmonary hypertension or at risk for increased intracranial pressure are excluded. Detailed inclusion and exclusion criteria are listed in table 1. Mechanically ventilated children are screened daily from Monday to Friday by study coordinators using the institutional PICU patient data monitoring systems (MetaVision Suite, Israel-iMDsoft Ltd., Tel Aviv, Israel/CGM Clinical—Phoenix, CompuGroup Medical Switzerland AG, Niederwangen, Switzerland). If eligible, a study coordinator and a physician contact the child’s parents or legal guardian(s) to explain the study and obtain prospective consent. Written informed consent is sought from parents or guardians and adolescent patients aged 14 years and older. If prospective consent cannot be obtained for an otherwise eligible child due to the emergency environment, study procedures are initiated if approved by an independent physician and consent is sought as soon as possible once the parent/guardian has had time to adapt to the emergency environment in the PICU (consent to continue, to be sought within 24 hours). No intervention or outcome data will be available for analysis from those where consent cannot be obtained. Withdrawal of consent does not affect subsequent medical assistance and treatment of the child. In case of withdrawal of informed consent, there is no further data collection. All data collected up to that point may be analysed in coded form and after the evaluation anonymised or deleted. Patients may be enrolled more than once during subsequent PICU admissions if the date of the second enrolment is at least 30 days after the date of the previous enrolment.

**Table 1 AT1:** Inclusion and exclusion criteria

Inclusion criteria	Exclusion criteria
Admission to PICU at the University Children’s Hospital Zurich Mechanical ventilation required for >60 min during PICU hospitalisation Arterial line required during PICU hospitalisation Age <18 years Weight >2 kg Informed consent provided by the participant or the participant’s parents or legal guardians, or in case of an emergency situation approval by a physician who is independent of the study	Substantial air leak around the endotracheal tube (>30%) Cyanotic heart disease Intracranial hypertension (ie, traumatic brain injury or patients admitted after neurosurgery) Pulmonary hypertension under treatment (ie, sildenafil or inhaled nitric oxide) Time from start of invasive mechanical ventilation until screening time >24 hours Previous enrolment in the trial in the past 30 days Inability of the parents or legal guardians to understand the study due to linguistic or cognitive reasons

Need for mechanical ventilation and need for an arterial line will be based on clinical decision of the treating physician. Previous enrolment refers to previous admission. PICU refers to the paediatric intensive care unit at the University Children’s Hospital Zurich.

### Randomisation and blinding

The randomisation schedule was computer-generated with variable block sizes (4, 6, 8 and 10) using a 1:1 allocation ratio and stratified by age as follows:

Neonates, defined as having a postnatal age <28 days if born at term (ie, born at ≥37 weeks of gestational age) or a postnatal age of <44 weeks of corrected gestational age if born preterm (ie, born at<37 weeks of gestational age).Older infants, children or adolescents, defined as a postnatal age ≥28 days if born at term or ≥44 weeks corrected gestational age if born preterm.

The randomisation and electronic allocation system is embedded in the trial’s Research Electronic Data Capture (REDCap) database,^14^ which ensures concealment of allocation. The randomisation sequence was generated by the data manager, who is not involved in recruitment or allocation. Based on our team’s previous experience using REDCap randomisation, we do not anticipate any challenges, and as such, plus the digital focus of the study, we do not have backup envelopes. Once eligibility is confirmed and consent is obtained from the patient, family or an independent physician, randomisation is performed by a study coordinator or physician and allocation is communicated electronically to the treating staff. Blinding is not possible due to the nature of the intervention. Eligible patients are enrolled in the trial after obtaining consent (time point 0), or consent to continue (figure 1) and randomisation.

**Figure 1 F1:**
[figure not shown]
Study design of the CoCO_2_ randomised controlled trial. COCO_2_, comparison of carbon dioxide control during pressure controlled versus pressure regulated volume controlled ventilation in children; ETCO_2_, end-tidal carbon dioxide; FiO_2_, Fraction of inhaled oxygen; MDSi, minimal dataset of the Swiss Society of Intensive Care; MV, minute vol; PC, pressure control; PEEP, positive end-expiratory pressure; PICU, Paediatric intensive care unit; PIM-2, Paediatric Index of Mortality version 2; Pinsp, peak inspiratory pressure; PRVC, pressure-regulated volume control; RR, respiratory rate; SpO_2_, peripheral oxygen saturation; VT, tidal volume.

### Interventions and treatment arms

The trial compares two ventilation modes: PC and PRVC. Both modes of invasive mechanical ventilation are part of routine standard care at the study hospital. Invasive ventilation is provided using the Bellavista 1000 ventilators (IMT Medical, Buchs, Switzerland/Vyaire Medical, Chicago, USA). The Bellavista brand label for the PC mode is ‘pressure support ventilation (PSV)’ and for the PRVC mode is ‘pressure support ventilation with TargetVent (PSV with TargetVent)’. Both ventilation modes provide pressure using a decelerating flow pattern. The difference between the modes is that in PC physicians set the inspiratory pressure (plus inspiratory time, respiratory rate and positive end-expiratory pressure (PEEP)), whereas in PRVC physicians set a target tidal volume (plus inspiratory time, respiratory rate, PEEP, as well as the upper and lower limits of pressure support), and an algorithm delivers pressure to achieve the target tidal volume based on lung compliance measured during previous breaths while remaining between the prescribed pressure limits. Deviations from the assigned mode are allowed based on the clinical judgement of the treating physician and will be captured. Measures to improve adherence include verbal reminders and placement of stickers indicating the assigned ventilation mode on the ventilation monitors.

### Study outcomes

This pilot study is designed to provide estimates of feasibility and physiological outcomes with high temporal resolution to assist in the planning of future trials.

The *primary feasibility outcome* is adherence to the assigned ventilation mode among enrolled patients, measured from randomisation to censoring (48 hours after randomisation, extubation, discharge from PICU, or death, whichever comes first) among enrolled patients. This is measured as the proportion of time under invasive ventilation spent in the assigned ventilation mode. Discontinuations from the assigned mode lasting 15 min or less are excluded. We set a threshold for adherence to the allocated mode of 80%, meaning that patients who are ventilated with the assigned mode during ≥80% of their time in the study are considered adherent.The *primary physiological outcome* is the proportion of time spent within the target CO_2_ range (normocarbia, defined as CO_2_≥35 mm Hg or 4.5 kPa and ≤45 mm Hg or 6 kPa) as measured by end-tidal CO_2_ (ETCO_2_) recorded by the ventilation device and transferred to the electronic health record system every minute from randomisation to censoring. This is calculated as the total number of minutes spent with ETCO_2_ within the target CO_2_ range divided by the total number of minutes ventilated from randomisation to censoring. Arterial blood gas analysis is the gold standard to assess ventilation; however, this is an invasive and intermittent measurement. Trends in ETCO_2_ are non-invasive, continuously available at bedside and serve as a proxy for changes in partial pressure of CO_2_ in arterial blood (PaCO_2_) in children and neonates.^15^*Secondary feasibility outcomes* describe recruitment and implementation aspects of the study (table 2). These include the number of patients who were screened, were missed, gave consent and were randomised and enrolled per month, reasons for protocol violations; and times from randomisation to protocol violation, from start of ventilation to screening, from start of ventilation to randomisation and from consent to randomisation. The technical feasibility of digital data extraction is assessed through the proportion of enrolled participants with complete primary and secondary outcome data extracted from the electronic patient records.*Secondary physiological outcomes* on hypocarbia, hypercarbia or both are calculated using time-weighted averages to account not only for the time spent outside the target CO_2_ range but also for the magnitude of the difference from the target CO_2_ range (table 2, figure 2). The oxygenation index measured using peripheral oxygen saturation (SpO_2_) and partial pressure of arterial oxygen (PaO_2_) are also secondary physiological outcomes. While ETCO_2_, transcutaneous CO_2_ and SpO_2_ are time series measurements, the PaCO_2_ and PaO_2_ are obtained from intermittent blood gas analyses. To assess the later intermittent measurements over study time, each value will be carried on until the time of the next measurement.^16^

**Table 2 AT2:** Outcome measures

Primary feasibility outcome	Adherence to the allocated ventilation mode among randomised and enrolled patients, measured from randomisation until censoring (at 48 hours since randomisation, extubation, discharger or death, whichever comes first).
Secondary feasibility outcomes	Number of patients who were screened, missed (screening failure), gave consent and were randomised/enrolled per month Reasons for protocol violations (time taken to obtain written informed consent exceeded 24 hours; written informed consent obtained but no data collected; patient randomised but did not meet study specified inclusion/exclusion criteria for enrolment in the study; patient randomised to an incorrect age group strata; patient randomised but ventilation mode received is not the same as the randomised allocation; other) Time from randomisation to protocol violation Proportion of enrolled participants with complete primary and secondary outcome data extracted from the electronic patient record Time from ventilation start until screening Time from ventilation start until randomisation Time between consent and randomisation
Primary physiological outcome	Proportion of time spent within the target CO_2_ range (normocarbia, defined as CO_2_ ≥35 mm Hg or 4.5 kPa and ≤45 mm Hg or 6 kPa) measured using end-tidal CO_2_ recorded every minute from randomisation until censoring.
Secondary physiological outcomes (figure 2)	Time-weighted average of hypocarbia (CO_2_<35 mm Hg or 4.5 kPa), from randomisation until censoring and measured using: continuous end-tidal CO_2_ intermittent arterial blood gas analysis continuous transcutaneous CO_2_ measurements calibrated with results of arterial blood gas analyses Time-weighted average of hypercarbia (CO_2_>45 mm Hg or 6 kPa), from randomisation until censoring and measured using: continuous end-tidal CO_2_ intermittent arterial blood gas analysis continuous transcutaneous CO_2_ measurements calibrated with results of arterial blood gas analyses Time-weighted average of hypocarbia and hypercarbia (ie, outside normocarbia, CO_2_<35 mm Hg or 4.5 kPa; or CO_2_>45 mm Hg or 6 kPa), from randomisation until censoring and measured using: continuous end-tidal CO_2_ intermittent arterial blood gas analysis continuous transcutaneous CO_2_ measurements calibrated with results of arterial blood gas analyses Oxygenation index, from randomisation until censoring and measured using: Peripheral oxygen saturation index (OSI): MAP * FiO_2_ * 100 / SpO_2_ (MAP=mean airway pressure, FiO_2_=fraction of inspired oxygen, SpO_2_=peripheral oxygen saturation) Arterial oxygenation index (OI): MAP * FiO_2_ * 100 / PaO_2_ (PaO_2_=partial pressure of oxygen in arterial blood)

CO_2_carbon dioxideFiO_2_fraction of inspired oxygenMAPmean airway pressurePaO_2_partial pressure of oxygen in arterial bloodSpO_2_peripheral oxygen saturation

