**Figure 2 F2:**
[figure not shown]
Graphical display and formulas used to calculate time-weighted averages for hypocarbia, hypercarbia and overall time spent outside the CO_2_ target range. The formulas account for both the severity of the hypocarbia/hypercarbia and time spent under hypocarbia/above hypercarbia in the numerator, divided by the total time until censoring for each patient. CO_2_, carbon dioxide.

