### Statistical analysis plan

The primary analysis will be performed on an intention-to-treat cohort. In case patients participate in the trial multiple times, the unit of analysis will shift from individual patients to individual admissions. This distinction will be appropriately handled through multilevel analyses. Results will be presented as effect estimates and 95% CIs, without the inclusion of p values. While missing data imputation will not be performed, outliers management in time series data will be addressed through the application of kernel smoothing.^24^

We will use descriptive statistics to summarise patient characteristics, adverse events and the distribution of feasibility and physiological outcomes. Categorical variables will be described using frequencies and percentages, continuous variables following a normal distribution using mean and SD and non-normally distributed variables using median and IQR. Normality will be assessed graphically with plots (histograms and Q–Q plots).

The analysis of both primary and secondary feasibility outcomes will be descriptive.

To analyse the primary physiological outcome, we will calculate the mean difference in the proportion of time spent in normocarbia (outcome) between the two ventilation modes (explanatory variable) using a linear mixed-effects regression model if the outcome is normally distributed. The stratification variable (age group) will be included as a fixed effect, and admissions will be nested within patients to account for correlated observations from patients potentially included more than once in the study. If the outcome has a skewed distribution, we will use quantile regression, also adjusting for stratification. The study is not powered to detect differences in physiological outcomes between the two ventilation models. Secondary physiological outcomes will be calculated using time-weighted averages as described in figure 2.

For physiological outcomes, we will conduct a per-protocol analysis including patients with adhere to the assigned ventilation mode for 80% or more of the study time.

As sensitivity analysis, we will calculate physiological outcomes using individual target CO_2_ ranges manually entered into the electronic information system by prescribing physicians when available, instead of standard normocarbia ranges. We will also assess the robustness of the results by testing different kernel sizes for smoothing and also present crude (not smoothed) results.

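### The primary physiological outcome counts ventilated minutes without an ETCO2 value as not normocarbic

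*Protocol article*

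**What the plan says.** **Primary physiological outcome.** The Study outcomes section gives the numerator as the "total number of minutes spent with ETCO_2_ within the target CO_2_ range". The denominator comes later in the same sentence, where this count is "divided by the total number of minutes ventilated from randomisation to censoring". ETCO2 comes from the ventilator and reaches the electronic record once a minute.

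**Missing values.** The Statistical analysis plan section says that "missing data imputation will not be performed". In the same sentence, "outliers management in time series data will be addressed through the application of kernel smoothing". Smoothing is given as a treatment for outliers; gaps are not mentioned.

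**Time-weighted averages.** The Figure 2 caption describes what is summed: "The formulas account for both the severity of the hypocarbia/hypercarbia and time spent under hypocarbia/above hypercarbia in the numerator". On the divisor, it says that this sum is "divided by the total time until censoring for each patient". The formulas themselves are in the figure, which is not shown.

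**Intermittent blood gases.** For PaCO2 and PaO2, "each value will be carried on until the time of the next measurement". No such rule is stated for ETCO2 or transcutaneous CO2.

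**Expected data loss.** The strengths and limitations box anticipates technical problems with data availability and says they will be documented. A secondary feasibility outcome reports the proportion of participants with complete primary and secondary outcome data.

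**The concern.** The two parts of the fraction are built on different sets of minutes. A minute in which the child is ventilated but no ETCO2 is recorded cannot enter the numerator and always enters the denominator. Without imputation it has the same effect as a minute of measured hypocarbia or hypercarbia. The outcome then mixes CO2 control with availability of the ETCO2 signal.

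This matters because the pilot exists to supply parameter estimates for later trials. Balanced loss lowers the mean and shrinks any true difference between arms. Loss that varies between patients also changes the standard deviation that a later sample-size calculation would use. Loss that differs between arms would look like an effect of ventilation mode. The planned sensitivity analyses (individual CO2 targets, different kernel sizes, unsmoothed results) leave the denominator as it is.

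**Working it through.** **The plan's own figure.** None is given for this outcome. The one computed result in the article concerns adherence: 47/60 = 78.3%, with a one-sided 95% lower limit of 67.8% (Clopper-Pearson) or 68.5% (Wilson). This agrees with the stated 78% and 68%, and it does not depend on the present point.

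**Inputs.** From the article: one reading per minute and at most 48 h, so at most 48 × 60 = 2880 minutes per patient; numerator and denominator as quoted; no imputation. Assumed, because the article gives neither: true share of time in range *r*, and share of ventilated minutes without ETCO2 *m*.

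**Step 1: random loss.** With *T* ventilated minutes, *T*(1 − *m*) have a value, and a share *r* of those is in range.

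- As written: *r* × *T*(1 − *m*) / *T* = *r*(1 − *m*)
- With valid minutes as denominator: *r* × *T*(1 − *m*) / [*T*(1 − *m*)] = *r*

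For a patient with the full 2880 minutes, *r* = 0.70 and *m* = 0.10, 2592 minutes have a value, and 0.70 × 2592 = 1814.4 are in range. As written: 1814.4 / 2880 = 63%. On valid minutes: 1814.4 / 2592 = 70%.

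| Assumed loss *m* | *r* = 60% | *r* = 70% | *r* = 80% |
|---|---|---|---|
| 5% | 57% | 66.5% | 76% |
| 10% | 54% | 63% | 72% |
| 20% | 48% | 56% | 64% |
| 30% | 42% | 49% | 56% |

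**Step 2: comparison of arms.** With equal loss, a true difference is multiplied by (1 − *m*), and no false difference arises. With equal true control (*r* = 0.70) and assumed loss of 5% against 15%, the result is 0.70 × 0.95 − 0.70 × 0.85 = 0.665 − 0.595 = 0.07. This is a false difference of 7 points against the arm with more loss. At *r* = 0.60 it is 0.57 − 0.51 = 6 points.

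**Step 3: spread.** If loss *M* varies between patients independently of time in range *R*, the variance of *R*(1 − *M*) is Var(*R*) × E[(1 − *M*)²] + E[*R*]² × Var(*M*). The first term shrinks the true variance; the second adds variation that comes only from signal availability.

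**Step 4: loss that is not random** (*r* = 0.70, *m* = 0.10).

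- All missing minutes truly out of range: as written 70%, which is correct; on valid minutes 0.70 / 0.90 = 77.8%.
- All missing minutes truly in range: as written 0.70 − 0.10 = 60%; on valid minutes 0.60 / 0.90 = 66.7%.

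The written definition is therefore the lower bound, in which every missing minute is out of range, used as the main estimate.

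**Step 5: time-weighted averages (conditional).** If an unmeasured minute adds nothing to the numerator and total time is the divisor, the result is the true value × (1 − *m*). With an assumed true mean excursion of 0.30 kPa and loss of 5% against 15%, the arms read 0.30 × 0.95 = 0.285 and 0.30 × 0.85 = 0.255 kPa. The arm with more loss now looks better controlled, the reverse of Step 2.

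**The case against.** **The handling of empty minutes is ordinary analysis-plan detail, and that plan is not shown.** Declining to impute could also mean dropping such minutes, and Table 2 can be read as referring to recorded minutes only. This lowers certainty about what will be programmed. It does not remove the point: the article does not defer the denominator but fixes it as ventilated minutes, and an analysis plan using valid minutes would contradict that sentence.

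**Some causes of loss may cancel.** Ventilation parameters and ETCO2 arrive through the same ventilator feed, so an interface failure may remove the minute from both parts of the fraction, and a disconnected minute may not count as ventilated. This stands. The clear remaining case is ventilation recorded while ETCO2 is not.

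**Smoothing may bridge short gaps.** It may, but the text offers it for outliers only, and crude results are also to be presented.

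**No loss rate is given.** This also stands. Both modes run on the same ventilator model, and nothing in the article shows that loss would differ by arm. The 5% against 15% case is an illustration.

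A reader might go further and infer that data loss makes CO2 control look better throughout. The article does not support that. In the primary outcome the direction is the opposite. For the secondary outcomes the inference rests on a caption whose formulas are not visible; an area computed between successive recorded values would span a gap. It cannot extend to PaCO2, which is carried forward, or to the oxygenation indices, which have no excursion term.

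**Conclusion.** The point holds for the primary physiological outcome. The stated numerator and denominator, together with no imputation, score a ventilated minute without ETCO2 as not normocarbic. Under random loss the outcome is *r*(1 − *m*): for a true 70%, a shortfall of 3.5, 7 or 14 points at an assumed 5%, 10% or 20% loss. The actual size is unknown, because the article states neither the loss nor the expected time in range.

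For the continuous ETCO2 and transcutaneous time-weighted averages, a bias towards better control follows only if the formulas match the caption and gaps are not bridged.

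Severity is moderate. A reader might infer that the decision to proceed to a larger trial is compromised; it is not, because that criterion rests on adherence to the assigned mode. The study is also declared not powered for physiological differences and reports no p values. What is affected is the mean, spread and between-arm estimate handed to future trials, which are among the pilot's stated products.

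**What to change.** 1. Define the primary physiological outcome as minutes with a valid ETCO2 value in range divided by ventilated minutes with a valid ETCO2 value.
2. For the continuous ETCO2 and transcutaneous time-weighted averages, divide by the time with a valid value of that signal, if the Figure 2 formulas do not already do so.
3. Report the fraction of ventilated minutes with a valid value per patient and by arm.
4. Add two sensitivity analyses of the primary physiological outcome, with missing minutes all out of range (the present definition) and all in range. At *r* = 0.70 and 10% random loss these give 63% and 63% + 10% = 73%, around a main estimate of 70%.

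The cost is a sentence in each outcome definition and a few lines of code. No new data are needed, so the change remains possible although enrolment has ended; it should be recorded as a change to the analysis definition. The small downside is the assumption that missing minutes resemble observed ones. Step 4 of the working shows that this can fail in either direction, which is why the two bounds should accompany the estimate.
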